### Assessments

All assessments are carried out by one researcher ([name]) who is not involved in the treatment of the patients. The bipolar disorder diagnoses according to ICD-10 are confirmed by a SCAN interview before inclusion of the patients. The patients are, regardless of randomization group, enrolled for a 9-month trial period and invited for outcome assessments by a blinded researcher ([name]) at baseline, after 4 weeks, after 3 months, after 6 months and after 9 months (Table 1).

At each visit with the researcher the assessments include the following: The severity of depressive and manic symptoms is measured using HDRS-17 item and YMRS, respectively, and psychosocial functioning is measured using the Functioning Assessment Short Test (FAST) [38]. The following questionnaires are fulfilled when visiting the researcher: perceived stress according to Cohen’s Perceived Stress scale [39], quality of life according to WHO Quality of Life-BREF (WHOQoL-BREF) [40], self-rated depressive symptoms according to Becks Depressive Inventory (BDI) [41–43], self-rated manic symptoms according to Altman Self Rating scale for Mania (ASRM) [44], recovery according to Recovery Assessment Scale (RAS) [45], medicine adherence according to Medicine Adherence Rating Scale (MARS) [46] and empowerment according to Rogers Empowerment Scale (RES) [47].

Furthermore, the patients are asked to show up fasting between 8–10 A.M. at baseline, after 4 weeks, 3 months, 6 months and 9 months when visiting the researcher and the following biological samples are collected: 1) Blood samples obtained by venipuncture, 90 ml in total and 2) a freshly voided morning spot urine sample (around 20 ml). The biological samples will be analyzed at the end of the trial for candidate biological markers that are potentially related to alterations in illness activity and affective state in bipolar disorder.

### Outcomes

#### Primary outcomes

Differences in clinically rated depressive and manic symptoms measured using HDRS-17 and YMRS, respectively, between the intervention group and the control group.Differences in depressive and manic symptoms measured using HDRS-17 and YMRS, respectively, between the intervention group and the control group in patients with presence of depressive and manic symptoms (defined as HDRS-17 > 0 or YMRS > 0) *at any given visit* with the researcher during the 9-month trial period.Differences in depressive and manic episodes defined as HDRS-17 ≥14 or YMRS ≥14 between the intervention group and the control group.

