### Hypotheses

Using a smartphone-based monitoring system for daily electronic self-monitoring including an integrated feedback loop on both subjective and automatically generated behavioural data on measures of illness activity (phone usage, social activity, physical activity, and mobility) (the Monsenso system) reduces the severity of depressive and manic symptoms and rate of depressive and manic episodes in adult patients with bipolar disorder more than standard treatment.

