**Table 1 Tab1:** **Outcome assessment overview- The MONARCA II trial**

	**SCAN** ^**a**^	**Baseline characteristics**	**Rating scales** ^**b**^	**Questionnaires** ^**c**^	**Clinical information** ^**d**^	**Biological samples** ^**e**^
Inclusion and baseline	x	x	X	X	x	X
Randomization (2:1) to using a smartphone with the MONARCA II system (the intervention group) or to use a smartphone for normal communicative purposes (the control group)						
4 weeks			X	X	x	X
3 months			X	X	x	X
6 months			X	X	x	x
9 months			X	X	x	x

^a^Schedules for Clinical Assessment in Neuropsychiatry interview (37).

^b^Depressive symptoms according to Hamilton Depression Rating Scale 17-item (29), manic symptoms according to Young Mania Rating Scale (30) and psychosocial functioning according to Functioning Assessment Short Test (FAST) (38).

^c^Perceived stress according to Cohen’s Perceived Stress scale (39), quality of life according to WHO Quality of Life-BREF (WHOQOL-BREF) (40), self-rated depressive symptoms according to Becks Depressive Inventory (BDI) (41–43), self-rated manic symptoms according to Altman Self Rating scale for Mania (ASRM) (44), recovery according to Recovery Assessment Scale (45), empowerment according to Rogers empowerment scale (47) and medicine adherence according to Medicine Adherence Rating Scale (MARS) (46).

^d^Number of affective episodes, number of contacts to clinicians and psychiatric emergency rooms, number of hospitalizations, medication status etc.

^e^Blood samples is obtained by venipuncture, 90 ml in total and a freshly voided spot urine sample is collected.

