#### Secondary outcomes

Differences in automatically generated behavioural data (objective data) collected from the smartphones (e.g. mobility, social and physical activity etc.) between the intervention group and the control group.Differences in the total number of days hospitalized between the intervention group and the control group.Differences in psychosocial functioning according to the FAST score between the intervention group and the control group.

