### Statistical methods

Data from all randomized patients are collected until dropout or the end of the trial period. Analysis will be carried out with an intention-to-treat (ITT) approach. The primary outcomes are differences in depressive and manic symptoms using HDRS-17 and YMRS, respectively, during the 9-month trial period. Analysis will be done employing a linear mixed effects model with random intercept for each participant and a fixed effect of visit number. Differences in outcomes between the intervention group and the control group will be analyzed, firstly in an unadjusted model (except for potential differences in baseline values of the outcome variable) and then in models adjusted for age and sex as possible prognostic variables.

Furthermore, analysis will be done employing a linear mixed effects model with random intercept for each participant and a fixed effect of visit on differences in HDRS-17 and YMRS in patients with presence of depressive and manic symptoms (defined as HDRS-17 > 0 or YMRS > 0) at a given time point during the trial period between the intervention group and the control group. Additionally, analysis of the primary outcomes of differences in depressive and manic episodes defined as HDRS ≥14 and YMRS ≥14 during the trial period will be done employing survival analysis with reasons for censoring being date of death or date of drop out.

Potential interactions between randomization group (intervention group or control group) and visit number in the analyses will be investigated and reported accordingly. The statistical threshold for significance is p ≤ 0.05 (two-tailed). Data will be managed by [name] and entered using Epidata® (Epidata Association, Odense, Denmark). All analyses will be done using STATA version 12 (StataCorp LP, College Station, TX, USA).

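### The primary episode outcome records whether HDRS-17 or YMRS is ≥14 at a follow-up visit, which depends on episode duration as well as onset, so it cannot by itself support a conclusion about the rate of episodes

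*Protocol article*

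**What the plan says.** The Hypotheses section of the protocol article states that the system "reduces the severity of depressive and manic symptoms and rate of depressive and manic episodes" more than standard treatment. The Abstract and the Objectives also speak of the rate of episodes, and the Abstract labels it primary. The sample-size section refers to the number of episodes.

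The Primary outcomes section defines the quantity compared: "Differences in depressive and manic episodes defined as HDRS-17 ≥14 or YMRS ≥14 between the intervention group and the control group". The sample-size and Statistical methods sections repeat the same threshold. No duration, onset or between-visit criterion is attached to it.

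The Assessments section fixes when the scales are rated: "At each visit with the researcher the assessments include the following: The severity of depressive and manic symptoms is measured using HDRS-17 item and YMRS". Those visits are at baseline, 4 weeks, 3 months, 6 months and 9 months. No other source of HDRS-17 or YMRS scores is described.

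Under Statistical methods, the episode analysis "will be done employing survival analysis with reasons for censoring being date of death or date of drop out".

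Table 1, footnote d, lists further information gathered at every visit: "Number of affective episodes, number of contacts to clinicians and psychiatric emergency rooms, number of hospitalizations, medication status etc". The episode outcome does not draw on these counts. Admissions do enter elsewhere, as a secondary outcome: "Differences in the total number of days hospitalized between the intervention group and the control group".

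**The concern.** A rate of episodes counts new onsets over time at risk. A visit-day threshold registers an episode only if the score happens to be at or above 14 on one of four follow-up days. The chance of that rises with the length of the episode, so the outcome combines onset rate and duration in one figure.

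This matters because the intervention could plausibly act on duration. Under the feedback loop, the study nurse reviews data two to three times a week and contacts patients or their clinicians when there are signs of deterioration. If that shortens episodes but prevents none, this outcome would show fewer episodes in the intervention group, and a report in the plan's own terms would call it a lower episode rate. Conversely, a real fall in the number of short episodes could be largely invisible. A patient whose episode falls between visits and who then drops out is censored with no episode recorded. The Discussion makes a lower rate of episodes part of the basis for wider use of the system, so the label affects the conclusion.

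**Working it through.** **The plan's own figures.** With the usual two-sample formula, n = 2(1.96 + 0.84)²σ²/δ² per group. For symptoms (δ = 3, σ = 7) this gives 85.5, so 86. For episodes (δ = 10%, σ = 23%) it gives 83.0, so 84, which agrees with the plan's 'about the same number' as 86. The figures reproduce, but they say nothing on whether a visit-day threshold measures a rate.

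**Visit gaps.** Taking 3, 6 and 9 months as weeks 13, 26 and 39, follow-up visits fall at weeks 4, 13, 26 and 39. The gaps are 4, 9, 13 and 13 weeks.

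**Share of episodes that coincide with a visit.** Assume onset is uniform over the 39 weeks and the score stays ≥14 for a fixed d weeks. An episode is registered if its onset lies within d weeks before some visit. The share is the length of the union of the intervals [v − d, v] over the four visits, cut at week 0 and divided by 39. The durations are assumptions.

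| d (weeks) | Weeks covered | Share |
|---|---|---|
| 2 | 2+2+2+2 = 8 | 8/39 = 21% |
| 4 | 4+4+4+4 = 16 | 16/39 = 41% |
| 6 | 4+6+6+6 = 22 | 22/39 = 56% |
| 8 | 4+8+8+8 = 28 | 28/39 = 72% |
| 12 | 13+12+12 = 37 | 37/39 = 95% |
| 13 or more | 39 | 100% |

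The share never rises as episodes get shorter. Below 13 weeks it falls; at 13 weeks or longer every episode meets a visit and the per-episode effect vanishes.

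**Effect of shortening alone, same onset rate.** Going from 8 to 4 weeks lowers the registered episodes by 1 − 16/28 = 43% with fixed durations. With exponential durations of mean 8 and 4 weeks, simulated shares are 54.6% and 35.3%, a fall of 1 − 35.3/54.6 = 35%.

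**The same on a per-patient scale.** Let patients start below threshold, so both arms begin alike, with onset rate λ per well-week and exponential durations of mean D weeks. Write π = λ/(λ + 1/D). The chance of being ≥14 at a visit t weeks after a below-threshold reading is p(t) = π(1 − exp(−(λ + 1/D)t)). The share of patients ever ≥14 at follow-up is 1 − [1 − p(4)][1 − p(9)][1 − p(13)]². With an assumed λ of 1.5 per well-year (1.5/52):

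- D = 8: π = 0.1875; p = 0.086, 0.141, 0.162; share 45%.
- D = 5: π = 0.126; p = 0.076, 0.110, 0.120; share 36%.
- D = 4: π = 0.103; p = 0.070, 0.095, 0.101; share 32%.

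Shortening from 8 to 4 weeks lowers the share by 1 − 31.9/44.9 = 29%. At 1.0 onset per well-year the shares are 33% and 23%, a fall of 31%. Shortening from 8 to 5 weeks at 1.5 per well-year gives about 9 points (45% to 36%). That is close to the plan's 10-point contrast of 50% against 40%, if that contrast is read as a share of patients, with no change in onset rate.

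**The case against.** Several stronger readings are tempting, and the article does not support them.

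- *Episodes and admissions between visits are lost to the trial.* They are not. Footnote d of Table 1 records both at every visit, and days hospitalized is a secondary outcome. They are absent only from the primary episode outcome.
- *Only the first event counts.* The article says survival analysis and no more. That term can include recurrent-event models, and such detail may sit in an unseen analysis plan. The point does not need it: any model fitted to visit-day readings inherits the dependence on duration.
- *The bias is 43%.* That is one assumed scenario. Other equally arbitrary assumptions above give 29% to 35%, and episodes of fixed length of 13 weeks or more give no per-episode effect.
- *The primary objective goes unanswered.* The hypothesis also covers symptom severity, analysed from HDRS-17 and YMRS by mixed models. Only the claim about rate is affected.

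The best defence of the plan is that the threshold is stated consistently and rests on named scales rated by a blinded researcher. Interval counts would be weaker as a primary outcome. Patients and their clinicians know the allocation, intervention patients keep daily records that may aid recall, and nurse escalation may itself affect admissions. Footnote d also states no episode criteria, onset dates or reference period. All of this stands, and it argues against replacing the outcome. It does not make a visit-day threshold a measure of rate.

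**Conclusion.** The point holds as one about what the episode outcome measures and what may be concluded from it. As defined, it is the presence of HDRS-17 or YMRS ≥14 at a follow-up visit, a joint product of onset rate and duration, while the Abstract, Hypotheses and Objectives claim an effect on rate. A treatment that only shortens episodes would appear to reduce them. At an unchanged onset rate the direction is firm for episodes shorter than the visit gaps. The size is not known: capture runs from 21% to 95% for assumed fixed durations of 2 to 12 weeks, and an assumed halving from 8 to 4 weeks lowers the detected frequency by roughly 29% to 43% depending on the model. The article gives no durations, onset rates or expected shortening. The change is worth making, because it is cheap and bears on a primary conclusion. It does not put the symptom outcomes in doubt.

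**What to change.** 1. Keep the blinded threshold outcome, but name it *HDRS-17 or YMRS ≥14 at a follow-up visit* throughout, including where the text now says rate or number of episodes.
2. State that no conclusion about episode rate will be drawn from this outcome alone.
3. Prespecify a supportive comparison by arm, per person-time, of the affective-episode and hospitalization counts already collected under Table 1, footnote d. Report admissions separately. State the episode criteria and the reference period (since the previous visit) used for the counts.

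The cost is mainly wording and one added analysis. Recruitment is under way and the article states that outcomes have not changed since the trial began, so the clarification should be dated, documented and made before any unblinded comparison. The threshold stays the same, so the plan's sample-size figures need no change on this account.

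The supportive counts have limits that should be stated with them: recall over up to about three months by unblinded patients, better records in the intervention arm, and admissions that the nurse's escalation may influence. They should support the threshold outcome, not replace it.

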#### Secondary outcomes

Differences in automatically generated behavioural data (objective data) collected from the smartphones (e.g. mobility, social and physical activity etc.) between the intervention group and the control group.Differences in the total number of days hospitalized between the intervention group and the control group.Differences in psychosocial functioning according to the FAST score between the intervention group and the control group.

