#### Subjective (self-monitored) measures of illness activity in the intervention group

The patients randomized to the intervention group, regardless the choice of smartphone, are prompted by an alarm in the Monsenso system at a self-chosen time during the day to evaluate subjective measures of illness activity on a daily basis. The following subjective (self-monitored) measures of illness activity are available for daily evaluation: mood (scored from depressive to manic on a scale from −3, −2, −1, −0.5, 0, +0.5, +1, +2, +3), sleep duration (number of hours slept per night, measured in half-hour intervals), medicine intake (taken as prescribed/ taken with changes (if changes, the patients are asked to specify these)/not taken), activity level (scored from very low to very high on a scale from −3, −2, −1, 0, +1, +2, +3), mixed mood (yes/no), irritability (scored from not present, present to some degree or present on a scale from 0, 1, 2), anxiety (scored from not present, present to some degree or present on a scale from 0, 1, 2), cognitive problems (scored from not present, present to some degree or present on a scale from 0, 1, 2), alcohol consumption (number of units consumed per day, 0 to +10 scale), stress (scored from not present, present to some degree or present on a scale from 0, 1, 2), menstruation for women (yes/no), individual early warning signs (yes/no), a number (unlimited) of personal parameters (created by the patients themselves), and a free-text note.

After midnight, the entered subjective (self-monitored) measures of illness activity are “locked” and further changes cannot be made. If the patients wish to change their subjective evaluation they can enter a second evaluation in addition to the initial one, and both of the subjective evaluations are then visible for the patient and the health care provider when logging on to in the Monsenso system. If the patients forget to evaluate the subjective measures it is possible to enter and evaluate retrospectively for up to two days. It is then noted in the Monsenso system that the subjective measures are collected retrospectively. Screenshots from the Monsenso software are presented in Figures 2 and 3. A user’s guide for the Monsenso system was developed and is handed out to all patients in the intervention group (can be obtained by contacting the first author).

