**The Monsenso system, self-monitored mood.**

#### Automatically generated behavioural data (objective data) on measures of illness activity in both the intervention group and the control group

All of the smartphones capable of collecting automatically generated behavioural data on measures of illness activity regardless of randomization group (intervention group or control group) collects as many automatically generated behavioural data on measures of illness activity (objective data) on a daily basis during the 9-month trial period as possible (different smartphones hardware and operating systems support different types of sensors) (Figure 1).

Examples of some of the automatically generated behavioural data on measures of illness activity collected by the smartphones: 1) phone usage measured as the amount of time the smartphones screen are turned on/off, battery usage, ambient light, and ‘proximity’ detection 2) social activity measured as the number of in- and outgoing phone calls and text messages, the duration of in- and outgoing phone calls, the length of the text messages, and the time of the day when the phone calls and/or text messages are made/send/or received 3) physical activity measured by the step counter in the smartphones, and 4) mobility based on the location estimation available in the smartphones (which again rely on e.g. GPD or GSM cell tower information depending on specific circumstances). Furthermore, speech activity is collected by extraction of different voice features during phone calls. Voice feature extraction will take place directly on the smartphones and no recording of the actual speech/conversation will take place.

Thus, we will be able to investigate correlations between automatically generated behavioural data on measures of illness activity and the severity of depressive and manic symptoms of all participants in the trial, using smartphones capable of collecting automatically generated data on measures of illness activity, including the ones allocated by randomization to the control group.

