
Actions by the study nurse as part of the feedback loop in the intervention group: In the case of signs of deterioration of a patient the MONARCA II study nurse a) contacts the patient and give advice on how to handle the situation b) (if the first action is not enough) asks the patient to contact his/her usual physician or other clinician c) (if the above actions are not enough, or if contact to the patient is not possible) contacts the patient’s usual physician or other clinician d) (if acute deterioration and/ or severe symptoms) contacts the psychiatric emergency service in Copenhagen, Denmark.

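### For phone usage, and probably for calls, the first secondary outcome counts phone use that the intervention itself generates in one arm, so a difference can arise with no change in illness

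*Protocol article*

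**What the plan says.** The Secondary outcomes section of the Protocol article lists first, as a comparison with controls, "Differences in automatically generated behavioural data (objective data) collected from the smartphones (e.g. mobility, social and physical activity etc.) between the intervention group". It does not separate use driven by illness from use driven by the trial.

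The section on automatically generated behavioural data describes the contents by example. Two of its four numbered domains matter here: "phone usage measured as the amount of time the smartphones screen are turned on/off, battery usage, ambient light" and "social activity measured as the number of in- and outgoing phone calls and text messages, the duration of in- and outgoing phone calls". The other two are physical activity (steps) and mobility (location). Every capable phone, "regardless of randomization group (intervention group or control group) collects as many automatically generated behavioural data".

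The arms are meant to use the phone differently:

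- **Self-rating.** Intervention patients "are prompted by an alarm in the Monsenso system at a self-chosen time during the day" to complete a daily self-rating of more than a dozen items.
- **System messages.** For patients with sensor-capable phones, the integrated feedback loop sends messages, for example advising contact with the study nurse.
- **Nurse contact.** At signs of deterioration the nurse "contacts the patient and give advice on how to handle the situation", and may then ask the patient to contact the usual clinician.
- **Controls.** The section on the smartphones has them use the phone for ordinary communication only.

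No section removes app time or trial contacts from the measures, and the Limitations section does not raise the issue.

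**The concern.** An outcome compared between arms should not be built partly from delivery of the treatment. Time spent in the app is screen-on time and drains the battery. A nurse call, or a call to a clinician that the nurse asked for, adds to call count and duration. All of this happens in one arm only, and the article labels the resulting data as illness activity.

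The Background reports that call numbers and durations correlated with HDRS-17 and YMRS scores in earlier work. Extra calls could therefore be read as a sign of changed illness. Nurse contacts are also triggered by deterioration, so in the intervention arm alone worse illness may itself raise call counts.

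At stake is the interpretation of a named secondary outcome. A mechanical increase could produce a spurious difference, or could hide a real fall in phone use.

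**Working it through.** **The plan's own figure.** The article gives no sample size or power for the smartphone outcome. Its only relevant figure is the 86 per group for symptoms (difference 3, SD 7, two-sided 5%, power 80%):

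n = 2 × (1.96 + 0.8416)² × 7² / 3² = 85.5, rounded up to 86.

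This agrees with the article, and 3 × 86 = 258. The figure is used here only to count patients.

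**Patients with sensor data.** About half are expected to use capable phones, and the phone is chosen before randomization (Randomization section). So about 172 × 0.5 = 86 intervention and 86 × 0.5 = 43 control patients supply these data. The 43 follows from applying the same 50% to controls.

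**Effect of a mechanical shift.** Suppose illness is the same in both arms and the intervention adds d standard deviations to a feature. For a two-sided z-test at 5%:

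s = √(1/86 + 1/43) = 0.187

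P(significant) = Φ(d/s − 1.96) + Φ(−d/s − 1.96)

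With d = 0 this returns 5.0%.

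**Screen time.** The minutes per day and the between-patient SD are assumptions; d = minutes / SD.

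| App use | SD 30 min | SD 60 min | SD 90 min |
|---|---|---|---|
| 2 min/day | d = 0.07, 6.5% | d = 0.03, 5.4% | d = 0.02, 5.2% |
| 5 min/day | d = 0.17, 14.5% | d = 0.08, 7.3% | d = 0.06, 6.0% |
| 10 min/day | d = 0.33, 43.1% | d = 0.17, 14.5% | d = 0.11, 9.1% |

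Example, 5 minutes and SD 30: d/s = 0.167/0.187 = 0.89, and Φ(−1.07) + Φ(−2.85) = 0.143 + 0.002 = 0.145.

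**Calls.** The weekly rate and the SD (calls per day) are assumptions; d = (calls per week / 7) / SD.

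| Extra calls | SD 1 | SD 2 | SD 4 |
|---|---|---|---|
| 0.5/week | d = 0.07, 6.7% | d = 0.04, 5.4% | d = 0.02, 5.1% |
| 1/week | d = 0.14, 11.9% | d = 0.07, 6.7% | d = 0.04, 5.4% |
| 2/week | d = 0.29, 33.4% | d = 0.14, 11.9% | d = 0.07, 6.7% |

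**Which features are exposed.**

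- Screen-on time and battery use: directly, through the daily self-rating.
- Calls: probably, through nurse and clinician contacts.
- Steps and mobility: no mechanical route.

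**The case against.** The strongest objection is that this is data processing, which an article leaves to a fuller document. The outcome is named only by domain, the listed features are examples, and the Statistical methods section specifies models for the primary outcomes only. Cleaning rules may exist elsewhere. That is fair as to detail. But the article does fix a between-arm comparison and does label the raw features as illness activity. Followed as written, it counts treatment delivery as patient behaviour, which is a bias and not just an omission.

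Other objections limit the point, and they stand:

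- The outcome's own examples are mobility, social activity and physical activity. Phone usage, where the mechanism is clearest, enters through the open-ended wording, although the Hypotheses and Objectives sections list it as illness activity.
- The nurse's channel of contact is not stated and contact follows no fixed schedule. The review two to three times a week is of data and is not a contact. Calls are therefore only a probable route.
- App use may displace other phone use instead of adding to it, which would shrink the shift.
- At the low end of the assumptions the false-positive rate stays close to 5%.

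A reader might infer three stronger things that the article does not support. First, that the whole outcome is compromised: steps and mobility have no mechanical link to the intervention. Second, that text counts are inflated: no section says the nurse sends texts, and the system messages are not described as text messages. Third, that the correlations of phone data with symptom scores are distorted: this is plausible, but it is a separate analysis and has not been shown.

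**Conclusion.** The point holds for phone usage (screen-on time and battery use) and probably for the call part of social activity. In these features a between-arm difference can arise with identical illness, so it cannot by itself be read as a change in illness activity.

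The upward direction follows from the design if trial-generated use adds to ordinary use. The size does not: no percentage inflation of screen time or contacts can be derived from the protocol. The central illustrations, about 6-15% for 5 minutes a day and about 5-12% for one call a week, rest on assumed usage and SDs and on 86 vs 43 capable phones.

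The primary outcomes are ratings by a blinded researcher and are not touched by this mechanism. The point concerns one secondary outcome, observed in about half the patients, and should be settled before its analysis.

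**What to change.** For the between-arm comparison, exclude time with the Monsenso application in the foreground, and calls or texts to and from the study nurse or other trial numbers, wherever the logs identify them. Texts are included as a precaution, since the channel of contact is unspecified.

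The article does not show that the foreground application or the other party to a call is recorded. If they are not, the phones could be set to flag both from now on, as recruitment is still open.

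Where trial-generated use cannot be separated, as with battery use, do not compare that feature between arms as a measure of illness activity. Base the outcome on features the intervention does not generate, such as steps and mobility.

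The cost is a filtering or flagging step, and some features may drop out of the between-arm comparison. No change to arms, visits or sample size is needed.
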